# EatSmart, a Web-Based and Mobile Healthy Eating Intervention for Disadvantaged People With Type 2 Diabetes: Protocol for a Pilot Mixed Methods Intervention Study

**DOI:** 10.2196/19488

**Published:** 2020-11-06

**Keywords:** type 2 diabetes, healthy eating, diet, low socioeconomic position, self-management, digitally delivered, internet, website, mobile phone, text message

## Abstract

**Background:**

People of low socioeconomic position (SEP) are disproportionately affected by type 2 diabetes (T2D), partly due to unhealthy eating patterns that contribute to inadequate disease self-management and prognosis. Digital technologies have the potential to provide a suitable medium to facilitate diabetes education, support self-management, and address some of the barriers to healthy eating, such as lack of nutritional knowledge or shopping or cooking skills, in this target group.

**Objective:**

This study aims to test the feasibility, appeal, and potential effectiveness of EatSmart, a 12-week, evidence-based, theoretically grounded, fully automated web-based and mobile-delivered healthy eating behavior change program to help disadvantaged people living with T2D to eat healthily on a budget and improve diabetes self-management.

**Methods:**

EatSmart is a mixed methods (quantitative and qualitative) pre-post design pilot study. Sixty socioeconomically disadvantaged people with T2D aged 18 to 75 years will be recruited. Participants will complete self-reported baseline assessments of their basic demographic and clinical data, dietary intake, dietary self-efficacy, and barriers to healthy eating. They will be provided with login access to the EatSmart web program, which includes six progressive skill-based modules covering healthy eating planning; smart food budgeting and shopping; time-saving meal strategies, healthy cooking methods, modifying recipes; and a final reinforcement and summary module. Over the 3-month intervention, participants will also receive 3 text messages weekly, encouraging them to review goals, continue to engage with different components of the EatSmart web program, and eat healthily. Participants will undertake follow-up assessments directly following the intervention 3 months post baseline and again after a 6-month postintervention follow-up period (9 months post baseline). Feasibility will be evaluated using the number of participants recruited and retained and objective indicators of engagement with the website. Program appeal and potential effects on primary and secondary outcomes will be assessed via the same surveys used at baseline, with additional questions asking about experience with and perceptions of the program. In-depth qualitative interviews will also be conducted 6 months post intervention to provide deeper insight into experiences with EatSmart and a more comprehensive description of the program’s appeal.

**Results:**

The EatSmart website has been developed, and all participants have viewed the modules as of May 2020. Results are expected to be submitted for publication in December 2020.

**Conclusions:**

This study will provide data to address the currently limited evidence regarding whether disadvantaged populations with T2D may benefit from digitally delivered behavior change programs that facilitate eating healthily on a budget.

**Trial Registration:**

Australian New Zealand Clinical Trials Registry, ACTRN12619001111167; https://anzctr.org.au/Trial/Registration/TrialReview.aspx?ACTRN=12619001111167

**International Registered Report Identifier (IRRID):**

DERR1-10.2196/19488

## Introduction

### Overview

Type 2 diabetes (T2D), which is defined by relative insulin deficiency resulting from pancreatic β-cell dysfunction and insulin resistance in target organs [1], is considered the epidemic of the 21st century [2]. T2D is a serious challenge for public health, affecting millions of people worldwide [3]. Globally, the number of people with diabetes has increased four-fold in the past three decades, and it was recognized as the ninth major cause of death in recent years [4,5]. According to the International Diabetes Federation, at the end of 2017, about 425 million people had diabetes, and this number is estimated to reach 628.6 million in 2045 [6]. Moreover, in the year 2018, 318 million adults were diagnosed with impaired glucose regulation that puts them at a high risk of developing diabetes in the future [7].

Individuals of low socioeconomic position (SEP), such as those with lower levels of education, working in low-status occupations, or on a low income, as well as ethnic minority groups, are disproportionately affected by T2D [8]. Unhealthy eating patterns and obesity are key risk factors for T2D [4,9,10]. Previous research has shown that compared with those of higher SEP, people of lower SEP commonly have more unfavorable eating patterns, with diets characterized by lower intake of fruits and vegetables and higher intake of less healthy discretionary foods and beverages [11-13]. While structural barriers, such as limited resources, low accessibility to higher quality foods and cost, contribute to these patterns, nutrition knowledge and skill deficits in cooking, lack of interest in cooking, lower prioritization of health during food selection, and low social support for healthy eating are also well-recognized hurdles with which these groups are struggling [14,15].

Existing initiatives to promote healthy eating among people with T2D include multicomponent face-to-face diabetes self-management classes, community health worker programs, and intensive case-management programs [16]. Traditionally, individuals participate in these programs in medical settings or at community health centers to acquire relevant knowledge about diabetes from clinicians, trained interventionists, or credentialed diabetes educators [17]. While such programs can effectively communicate health information to people with diabetes, they are limited in terms of sustainability and scale [18-22]. Time and access requirements preclude the ability of many individuals to attend multiple educational sessions [23-25]. Such intensive programs also incur high costs related to hiring, training, and maintaining educators, which not all practices are resourced to routinely provide [26].

Driven by advances in web-based technologies and requests by people with T2D for easily accessible information and ongoing support, digitally delivered programs potentially offer a convenient and efficient platform to facilitate the delivery and increase the reach of the self-management support needed by disadvantaged people with T2D [27]. Computers, laptops, and mobile phones or smartphones, hosting mobile applications (apps), are commonly used technologies for delivering digital programs [24]. These programs are secure and cost-effective and allow for the delivery of support in a way that is responsive, transactional, and participatory, and accordingly, more persuasive [17,28]. Furthermore, these programs can be easily distributable since they are not limited to a specific location and can be used in clinics, community health centers, home, or on the move at any convenient time [24,27,29]. With the advent of digital technology programs for health, there have been concerns about creating a digital divide, in which people of low SEP have lower access to the internet and mobile devices compared with higher socioeconomic groups [30]. However, more recent studies have demonstrated that the digital divide is gradually diminishing as the internet and mobile technologies have become more accessible to people from different SEPs [31]. Previous studies with low-income populations, including those with T2D and other chronic conditions, showed that a high proportion of participants knew how to use computers or mobile phones and were willing to expand their knowledge of how to use these technologies and find health information via the internet [32-35]. Moreover, it has been suggested that technology can efficiently play a role in bridging the digital divide and serve traditionally “hard to reach” populations. Thus, technology may provide a unique opportunity to decrease health disparities in underserved populations [31].

Previous reviews suggest that digital-based interventions show promise in increasing knowledge and improving diabetes self-management activities, including medication adherence, engagement in physical activity, and healthy eating behaviors in individuals living with T2D [22,27,36-40]. For example, in a review by Boren et al [41], 18 of 21 studies, which used computerized learning technologies to engage and empower people in diabetes self-management, showed positive outcomes in improving 49 out of 112 diabetes outcomes. They stated that while patients’ self management-related behaviors are crucial in diabetes control, computerized learning technology programs can play a major role in improving self-efficacy and diabetes self-care [41].

While digital interventions continue to be developed and researched, their potential for improving diabetes self-management among people of low SEP remains poorly investigated [36], and few have explored the efficacy of these interventions specifically on dietary and healthy eating behaviors [25,42-44]. One example is a study by Arora et al [44], who investigated the effects of educational and motivational text messages on improving healthy eating behaviors, exercising, medication adherence, and foot checks. That intervention led to a daily increase in eating fruits/vegetables by 26.5% and improved diabetes self-efficacy and medication adherence in resource-poor, inner-city patients with diabetes. Another example is the eCare We Care program by Moussa et al [25]. In that study, researchers examined the effect of an evidence-based web program on diabetes knowledge development and skill-building in African American adults with low diabetes literacy [25]. Their findings indicated that the program improved the diabetes and nutritional knowledge of participants [25]. Glasgow et al [45] also investigated the effect of an internet-based diabetes self-management program, with and without additional support, on improving healthy eating, physical activity, and medication taking. Their program improved health behaviors significantly compared to usual care over the 12 months (Cohen *d* for effect size .09-.16) [45].

Although these limited studies show promising results in improving dietary behaviors, they were all heterogeneous in scope. For example, they either concentrated on single nutrition-related health outcomes (eg, weight loss or glycemic control), or combined multiple health behaviors (eg, diet, medication adherence, and physical activity), and utilized different modes of intervention delivery (eg, website, text messages). Therefore, study findings are difficult to integrate and interpret, and there is a need for further research into how disadvantaged populations with diabetes may benefit from digital approaches and whether these programs are feasible, appealing, and can produce long-term and sustainable effects. The EatSmart program was developed to address this gap by designing and evaluating a theoretically grounded, evidence-based web- and phone-delivered healthy eating behavior support program to enable disadvantaged people with T2D to strengthen important skills necessary to eat healthily at low cost.

This project is important as it involves a simple and practical approach tailored to the needs of the many people with T2D who struggle to eat healthily in the context of socioeconomic disadvantage. The program may augment existing clinical management by integrating with people’s daily self-management practices of T2D. It also has the potential to reach larger numbers of people with T2D, regardless of geographic location. Moreover, it is designed to be sustainable without intensive ongoing clinical involvement. EatSmart addresses the critical issues of inequities in diabetes-related self-management and associated morbidity.

### Hypothesis

We hypothesize that delivery of the 12-week EatSmart program is feasible, appealing to participants, and effective in improving healthy eating behaviors and related attitudes. Specifically, we hypothesize that EatSmart will lead to high program satisfaction and engagement and improvements in self-reported intakes of vegetables, fruits, and foods aligned with dietary recommendations. It will also reduce self-reported intakes of discretionary noncore foods, increase self-efficacy, and reduce barriers to selecting and preparing a balanced healthy diet.

### Ethics Approval

Ethics approval has been granted by Deakin University’s Human Research Committee and the Western Health Low-Risk Ethics Panel, approval number 49763; version 4, dated 15 March 2019. All participants will be provided with an information sheet explaining the project aim and will be requested to sign a written informed consent form before participating (Multimedia Appendices 1-3).

## Methods

### Study Design

EatSmart is a mixed methods (quantitative and qualitative) pre-post design pilot study, which is appropriate for evaluating the feasibility, appeal, and potential effectiveness of a novel intervention. Pilot studies are crucial for examining the acceptability of new interventions and improving their delivery to support the future success of more intensive and larger randomized controlled trials [46].

EatSmart focuses on people with T2D who attend diabetes clinics in Melbourne’s western suburbs, which, according to the Australian Bureau of Statistics Socioeconomic Index for Areas index of relative advantaged/disadvantaged, comprises a relatively disadvantaged area.

### Study Population

#### Sample Size Estimation

A sample of N=60 (conservatively assuming up to 33% drop-out) has been selected for this pilot study. As this is a pilot study, no formal power calculation was conducted, and this sample size was determined pragmatically to provide adequate data on potential effects on key outcomes, sample variability, recruitment rates, and retention. This number is also adequate for generating rich qualitative and contextual data on intervention engagement, feasibility, and appeal to inform future larger studies.

#### Participant Recruitment

Sixty people with T2D will be recruited from two outpatient diabetes clinics located at Sunshine Hospital in Melbourne, Australia. Participant recruitment strategies involve (1) distribution of program flyers at diabetes clinics’ waiting rooms and to diabetes nurses and specialist offices in Sunshine Hospital; (2) in-person presentations by diabetes educators or researchers at hospital meetings and diabetes-related events; and (3) face to face recruitment of eligible individuals in diabetes clinic waiting rooms by EatSmart researchers.

For postintervention interviews, patients with T2D who participated in EatSmart and completed the 3-month intervention will be invited by telephone, text message, or email to complete a semistructured interview of up to 40 minutes via telephone or Zoom. Recruitment will be successive until no new themes appear (thematic saturation). Up to ten health care providers from Sunshine Hospital diabetes clinics will also be invited by email to take part in a confidential semistructured telephone or Zoom interview of up to 30 minutes.

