Feasibility and engagement will be evaluated by the number of participants recruited/retained, numbers accessing the website, logins and duration of website use, pages engaged with, and numbers receiving/reading the text messages [61]. For this purpose, web tagging is applied to the EatSmart website to record usage systematically. Tagging logs user interaction with particular program features and can provide real-time and historical statistics on engagement [62]. Website analytics allow us to identify whether portal login and usage are continuous, declining, or fluctuating during the intervention and follow-up period. In this intervention, we will consider adherence to the program to be confirmed by at least 66% of participants completing the study. We will also assess the number of website modules visited, as well as text messages read. While there is no set definition of feasibility in the literature for this context, we would consider the approach feasible if participants engage with the majority of materials (ie, on average more than 50% of website pages and text messages). However, we will also explore reasons for lower engagement levels through our semistructured interview to improve the materials for future larger studies. Program appeal, usability, and participants’ satisfaction will be assessed by self-report survey questions developed for this study. These include three statements with Likert scale responses and 11 open-ended qualitative questions about using the educational materials, useful features of the website and the messages, and liked and disliked aspects of the EatSmart program.

Participants will complete all self-report surveys, either web-based or telephone-assisted, at baseline and again at 3 and 9 months. The data capture and management tool REDCap (Research Electronic Data Capture) [63] will be used to collect data. Data will be entered automatically by the participant, via an individualized hyperlink or manually (by the research fellow), into REDCap. The data is stored, housed, and backed up within Deakin University in a database that can only be accessed via three layers of security (university firewalls, institute limitations, and project manager login).

Data on program appeal, usability, and participant satisfaction will be supplemented by semistructured interviews at 6 months post intervention to explore longer term maintenance of any behavioral or attitudinal changes.

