At 9 months post baseline, participants will be invited by telephone, text message, or email to complete a one-on-one semistructured interview of up to 40 minutes via telephone. Recruitment for interviews will be successive until no new themes appear (thematic saturation). However, based on other qualitative reports in the same area [64-66], we do not expect to recruit fewer than 25 participants. Interview methods are useful for gaining specific information while allowing participants to freely share their viewpoints [62]. These interviews will be conducted to understand participants’ experiences of the EatSmart program and answer questions about whether, how, and why the intervention modules created long-lasting behavioral changes. The researcher will use a discussion guide of open-ended questions, and the interview will be audio recorded to ensure all verbal data are captured. The researcher will also write notes after the interview to document related nonverbal data. Participants will answer questions about the various parts of the website, text messages, and content presented within the intervention, their perceived capability for action within their personal situation, and any subsequent healthy eating-related changes.

These interviews will add to the program feedback from the surveys and create a base for understanding the characteristics of patients for whom these healthy changes occur and last. These data will provide us with insight into contextual factors that promote engagement.

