Furthermore, a thematic analysis will be employed for open-ended surveys to identify key program likes and dislikes. For qualitative measures from interviews, audiotapes of the interviews will be transcribed verbatim and de-identified. Transcripts will be imported to NVivo software to enable coding of the interview data and expedite the organization of codes into themes and subthemes. Two researchers will do line-by-line coding on three initial transcripts and then meet to discuss the development of preliminary conceptual themes and subthemes. These initial conceptual themes will then be applied to subsequent transcripts. Open discussions within the research team will resolve discrepancies in data interpretation. The coding process will continue until saturation, such that no further codes or categories can be found in the data. Thematic analysis will be used to describe why and among whom the program works best [69]. Qualitative results will be reported according to consolidated criteria for reporting qualitative research (COREQ) [70]. Incorporation of quantitative and qualitative analyses will thus happen at multiple stages in the evaluation of the program. Results from our different data sources will be combined and then interpreted to improve the validity of our conclusions.

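### People who leave before 3 months are not invited to the interviews meant to explain lower engagement and for whom the program works; the protocol states the invitation rule in two ways and does not define completion.

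*Protocol article*

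**What the plan says.** The protocol article describes who is invited to the participant interviews in two places.

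- Participant Recruitment sets a condition: "patients with T2D who participated in EatSmart and completed the 3-month intervention will be invited by telephone, text message, or email". Recruitment then proceeds one after another until thematic saturation.
- Outcomes and Measures gives no such condition: "At 9 months post baseline, participants will be invited by telephone, text message, or email to complete a one-on-one semistructured interview". It adds that the team does not expect fewer than 25 interviewees.

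The same interviews are given these tasks, among others:

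- on engagement, in Outcomes and Measures: "we will also explore reasons for lower engagement levels through our semistructured interview to improve the materials for future larger studies";
- on who benefits, in the same section, to "create a base for understanding the characteristics of patients for whom these healthy changes occur and last";
- in the analysis, under Statistical Analysis: "Thematic analysis will be used to describe why and among whom the program works best".

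The Intervention section gives participants no usage target. It pays the 3-month voucher to everyone who completes the post-intervention assessments, whatever their level of engagement. The article does not define what completing the 3-month intervention means.

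**The concern.** Someone who leaves a digital program in its first weeks is among the best sources on why people stop using it. Under the rule in Participant Recruitment that person is removed before interview sampling starts. Saturation is then judged among those who remain, and saturation in that group carries no information about the reasons of those who left. A description of among whom the program works best also lacks its natural contrast if those who gave it up are not heard.

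The article presents the pilot as a way to test acceptability and improve delivery before a larger trial, and its Discussion names high attrition as a common problem in eHealth studies. If the interview findings come only from people who stayed, readers may take them to apply to everyone enrolled, and a later trial may be designed around them. The quantitative primary outcome is not touched by this point.

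**Working it through.** **Does the drop-out allowance agree with the other figures?** The inputs are in Sample Size Estimation ("A sample of N=60 (conservatively assuming up to 33% drop-out) has been selected for this pilot study") and Outcomes and Measures ("adherence to the program to be confirmed by at least 66% of participants completing the study").

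- Expected to remain at the maximum drop-out: 60 × (1 − 0.33) = 40.2, about 40.
- Expected to leave: 60 × 0.33 = 19.8, about 20.
- Adherence criterion: 0.66 × 60 = 39.6, about 40.
- Inflating 40 for drop-out: 40 / (1 − 0.33) = 59.7, which rounds up to 60.

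The sample size, the drop-out allowance and the adherence criterion agree. There is no power calculation to reproduce, and the point does not depend on one.

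**How many people could the rule keep out?** The 33% is an upper limit with no time point attached, and follow-up runs to 9 months. Only those who leave before 3 months are affected. The 10% and 20% rows are assumptions, to show the range.

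| Leave before 3 months | Not invited, of 60 | Remaining | 25 interviews as share of remaining | Non-completers expected if 25 were drawn in proportion from all 60 |
|---|---|---|---|---|
| 10% (assumed) | 6 | 54 | 25/54 = 46% | 25 × 0.10 = 2.5 |
| 20% (assumed) | 12 | 48 | 25/48 = 52% | 25 × 0.20 = 5 |
| 33% (protocol maximum, all before 3 months) | about 20 | about 40 | 25/40 = 62.5% | 25 × 0.33 = 8.25 |

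Under the rule in Participant Recruitment, the number of non-completers interviewed is 0 in every row. In every row, 25 interviews are 25/60 = 42% of those enrolled.

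**Who is kept out, and who is not?** This turns on the undefined term.

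- If completing means reaching the 3-month point or its assessment, a person who seldom logged in but stayed can be invited. Only early leavers are kept out.
- If completing means working through the modules, low users are kept out as well.
- If the wording in Outcomes and Measures governs, nobody enrolled is kept out.

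The article does not say which applies.

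**Does another described source ask early leavers why they left?**

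- Statistical Analysis compares the characteristics of those who exit early with those who complete. This shows who left, not why.
- Web logs show how much each person used the site, not why use stopped.
- The open-ended appeal questions are in the follow-up surveys, which a person who has left the study would not be expected to fill in.
- Provider interviews report patients' views at second hand.

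None of these puts the question to the people concerned.

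**The case against.** The strongest reply is that leaving the study and using the program little are different things, and the protocol keeps them apart. Adherence is tied to completing the study; feasibility is judged by the share of pages and messages engaged with. The promise is to explain lower engagement, not drop-out, and that can be met in part by interviewing people who stayed but used little. This stands. A reader might infer that everyone who disengaged is excluded by rule. The documents do not support that, because no usage minimum is set and completion is undefined.

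Second, the broader wording in Outcomes and Measures may be the operative one, in which case no one is excluded; or it may be shorthand for the stricter wording. Either is possible. This weakens any claim of a firm exclusion, but it is also why the two sections must be reconciled.

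Third, much of the interviews' stated purpose is the longer-term maintenance of change, for which people who finished are a suitable group. That is fair. The difficulty lies with the further aims on engagement and on who benefits.

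Fourth, the abstract reports that all participants had viewed the modules by May 2020, which does not suggest a large group who never used the program. It does not say how many stayed to 3 months, so it lowers the likely size without removing the point.

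Finally, a reader might conclude that appeal and acceptability will be overstated. That direction is plausible when only those who stay are asked, but nothing in the documents shows it. Requiring saturation within a low-engagement stratum is likewise one defensible design among several, not something the protocol gets wrong by omitting.

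**Conclusion.** The point holds in a limited form. The rule in Participant Recruitment leaves people who exit before 3 months out of the interviews, while the article assigns those interviews aims that need their views and describes no other step that asks them. This is a stated sampling rule, not detail left to a fuller document.

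The size is at most about 20 of 60. That figure assumes that the protocol's maximum drop-out occurs and that all of it falls before 3 months; with less or later drop-out the number is smaller. The point further assumes that the Participant Recruitment wording governs over the looser wording elsewhere. Whether low users who stayed are also affected cannot be settled from the article. The point should be corrected because it concerns a stated purpose of the qualitative arm, but it does not undermine the quantitative results.

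**What to change.** - Reconcile Participant Recruitment with Outcomes and Measures by dropping the completion condition. Invite all enrolled participants who still consent to contact, including early leavers.
- Use the web logs already being collected to make sure that low engagers are among those approached.
- State what completing the 3-month intervention means, so that readers can tell who is described as a completer.
- If interviews can no longer be extended, state that the findings on appeal, reasons for lower engagement and among whom the program works best apply to completers only. This may be the realistic option: recruitment ended in February 2020 and data collection was planned to run through October 2020.

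The cost is an amendment to the invitation wording and a few interview vouchers of AU $20 each. Even if all of at most about 20 leavers were interviewed, that is 20 × 20 = AU $400. The interview consent form is not shown, so the extent of any ethics amendment cannot be judged here. Response among leavers is likely to be lower, and the number approached and interviewed in that group should be reported.
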